## Introduction

Preterm birth, defined as birth before 37 weeks of gestation, is a leading cause of child morbidity and mortality. According to the World Health Organization, ~13 million babies are born preterm each year globally, which equates to more one premature birth for every ten deliveries. Specifically, in Nordic countries, the prevalence of preterm birth is estimated to be around 5.8%. Due to rapid advancements in obstetrics and neonatal care, most of these preterm babies have a better survival rate; however, they are more prone to cognitive deficits and neurodevelopmental disorders, such as ADHD, which exerts a heavy burden on affected families, society and to the health care system.

Preterm birth is associated with poor cognitive abilities. However, studies so far have mainly focused on children born very preterm (< 32 weeks of gestation) or extremely preterm (< 28 weeks of gestation), even though children born moderate to late-preterm (32 – 36 weeks of gestation) make up a substantial proportion of preterm birth groups. Compared to those born at term, children born moderate to late preterm are more prone to acute morbidity conditions such as respiratory distress, temperature instability, and neonatal hypoglycaemia. Despite this, these babies have been overlooked by the perinatal community, with extensive research mainly focused on children born extremely/very preterm. Recent evidence suggests that those born moderate-to late preterm and early-term, also at high risk of cognitive difficulties compared to their term born peers, yet studies have produced inconsistent results. For example, some studies have shown lower cognitive functioning in the moderate-to late preterm group during childhood, while others have shown no differences.

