## Study objectives

The aims of this study are two-fold:

- Investigate the association between preterm and early-term births on cognitive outcomes during mid-childhood; and assess the extent to which these associations can be explained by unmeasured genetic and environmental factors.
- Investigate the association between weeks of gestation and cognitive outcomes during mid-childhood; and assess the extent to which these associations can be explained by unmeasured genetic and environmental factors.

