## Hypothesis

Children born preterm is independently associated with poor cognitive abilities, with larger effect size for lower gestational ages.

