### 196 Covariates

197 Age of a child

198 Sex assigned at birth

199 Socio-economic status (based on PCA – total household income, highest parental education, and  
200 neighbourhood quality) (See appendix – page 15)

201 Polygenic scores (See appendix – page 15)

202 20 Principal components to account for the possibility of population stratification within the Add  
203 Health European-ancestry subsample in the same model.

204 Maternal factors (Hypertension, diabetes, placental problems, maternal age, infections, C-section,  
205 alcohol consumptions, tobacco usage, and mental health problems).

206 Multiple correspondence analysis (MCA) will be applied and components with over 60% of variance  
207 will be used.

208 Neonatal factors (Dyspnea, convulsion, jaundice, oxygen support, NICU). MCA will be applied.

209 Child factors (puberty).

210 Scanner sites as recommended by ABCD

211

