## Statistics

Maternal and child characteristics will be summarized using means and standard deviations for continuous variables and frequencies with counts for categorical distributions. To compare the demographic and clinical characteristics between children born preterm, early-term and born at full-term, independent samples t-test and  $\chi^2$ /Fisher exact tests will be employed. Missing covariates will be imputed through multiple imputations by chained equations with the predictive mean matching method using the MICE package in R.

Hierarchical logistic/linear regression model will be used to investigate the relationships between preterm birth and behavioural/brain outcomes. Model 1: Adjusted for age of child, sex, SES, Polygenic scores, 20 PCs, and scanner sites; Model 2: Model 1 + Maternal factors; and Model 3: Model 2 + Neonatal factors; Model4: Model 3 + child factors

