### **Primary analyses:**

- Linear regression model will be used to investigate whether the one-factor (intelligence) differ between preterm birth, early-term birth and full-term birth (presented as standardized beta and 95% CI)

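### The primary 0.05 test is not tied to one of the four nested models, and two of the four adjust for post-birth variables

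*SAP*

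**What the plan says.** The Hypothesis section states: "Children born preterm is independently associated with poor cognitive abilities, with larger effect size for lower gestational ages". It does not say whether independence refers to a total effect of gestational age or to a direct effect that excludes neonatal illness.

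Under Statistics, Model 1 adjusts for age, sex, SES, polygenic score, 20 genetic principal components and site. The sequence then continues: "Model 2: Model 1 + Maternal factors; and Model 3: Model 2 + Neonatal factors; Model4: Model 3 + child factors". Under Covariates, the neonatal block is given as "Neonatal factors (Dyspnea, convulsion, jaundice, oxygen support, NICU). MCA will be applied", and puberty is the only child factor.

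Under Primary analyses: "Linear regression model will be used to investigate whether the one-factor (intelligence) differ between preterm birth, early-term birth and full-term birth". No model number is attached. The text under Exploratory analyses sets the primary significance level at 0.05 without correction. The planned Table 2 is to hold the primary results, again without naming a model.

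**The concern.** Two gaps combine. First, the plan defines four coefficients for each gestational-age contrast and does not say which one the primary test uses. The data were collected in 2016–2018, so prespecification is the main protection against choosing a model after seeing the results.

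Second, the four models do not estimate the same quantity. Models 1 and 2 leave in whatever part of the association runs through neonatal illness; Models 3 and 4 remove it. A reader looking for the test of an independent association may well turn to the most adjusted model. If the total effect is the target, that model answers a different question and can make a real association look small or absent.

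**Working it through.** **Step 1: is a primary model named?** The Statistics, Primary analyses, Exploratory analyses and Planned Figures and Tables sections give four models, one linear regression, one significance level and one results table. None of them links the test to a model. The SAP states no sample size, power or effect size for this comparison, so there is no figure of its own to reproduce.

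**Step 2: are the added variables downstream of the exposure?** All five neonatal items and puberty come after gestational age is fixed. For the respiratory items the SAP supplies the link itself: compared with term-born children, "children born moderate to late preterm are more prone to acute morbidity conditions such as respiratory distress, temperature instability, and neonatal hypoglycaemia". It makes no such statement about jaundice, convulsion, NICU or puberty. Those are post-exposure by timing; whether they mediate is an assumption.

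**Step 3: how large could the over-adjustment be?** All inputs here are assumptions: 15% preterm; a single binary neonatal-illness variable with probability about 60% in preterm and 8% in other children (risk difference RD = 0.52); total effect −0.20 SD; effect of neonatal illness on cognition b = −0.1, −0.2 or −0.3 SD. In a linear model with no unmeasured cause shared by illness and cognition:

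adjusted coefficient = total − b × RD

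- b = −0.1: −0.20 + 0.1 × 0.52 = −0.148; loss 0.052/0.20 = 26%
- b = −0.2: −0.20 + 0.2 × 0.52 = −0.096; loss 0.104/0.20 = 52%
- b = −0.3: −0.20 + 0.3 × 0.52 = −0.044; loss 0.156/0.20 = 78%

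A simulation with n = 1,000,000 gave −0.147, −0.099 and −0.049 SD, so the loss is roughly a quarter to three quarters.

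**Step 4: is the direction certain?** The simulation was repeated with an unmeasured factor that raises the chance of neonatal illness and shifts cognition by 0.2 SD per SD. RD was then about 0.49 and the total effect stayed at about −0.20 SD.

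| b | True direct effect | Adjusted, factor lowers cognition | Adjusted, factor raises cognition |
|---|---|---|---|
| −0.1 | −0.151 | −0.082 | −0.228 |
| −0.2 | −0.102 | −0.031 | −0.173 |
| −0.3 | −0.054 | +0.012 | −0.124 |

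The coefficient can pass the null, or with a weak mediator move away from it (−0.205 total to −0.228 adjusted). In every row it also misses the true direct effect, so calling the target a direct effect would not rescue Models 3 and 4 without attention to such common causes.

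**Step 5: what does a free choice of model do to the error rate?** If the four tests were independent, the chance of at least one false positive would be 1 − 0.95⁴ = 0.185, with an upper bound of 4 × 0.05 = 0.20. Nested models are strongly correlated. In a null simulation (2,000 replicates, n = 3,000, 15% preterm), any-of-four significance for one contrast occurred at 0.072 to 0.078, with a Monte Carlo standard error of √(0.075 × 0.925/2000) = 0.006. The inflation is modest. The larger problem is the one in Step 3: the models estimate different quantities.

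**Limits.** The simulations use a binary exposure and one binary mediator. The SAP would enter multiple correspondence analysis (MCA) components of five items and compares several gestational-age groups. The figures show a plausible scale and do not predict the trial's result.

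**The case against.** The strongest defence is that the sequence of models has a purpose. Study objectives ask the analysis to "assess the extent to which these associations can be explained by unmeasured genetic and environmental factors", and the Introduction lists postnatal factors among those whose separate contribution to cognition is worth exploring. Adding maternal, neonatal and child blocks in turn is a recognisable way to do that. This stands as a reason to fit Models 3 and 4. It is not a reason to leave them eligible for the primary test: the SAP plans no mediation analysis and does not say how a change from Model 2 to Model 3 would be read.

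A reader might also infer several stronger points that the SAP does not support:

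- That the association as planned is biased toward the null. This concerns Models 3 and 4 only, depends on a total-effect target, and is the expected direction, not a certain one (Step 4). Nothing says Model 4 decides the hypothesis.
- That a single percentage describes the loss. The SAP gives no prevalences or effects, so only a range under stated assumptions is defensible.
- That attenuation is steepest at the lowest gestational ages and so hides the hypothesised gradient. This is plausible, but the SAP gives no rates by gestational age and the simulations did not test it.
- That puberty is a consequence of preterm birth. Only its timing is established.
- That four candidate p-values carry the error of four independent tests. They do not (Step 5).
- That Model 2 contains only pre-birth variables. The Appendix builds SES from household income over the preceding year and the deprivation index of the primary residence, so it is a current measure.

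**Conclusion.** The point holds in this form. The primary test is not tied to a model, the effect of interest is not defined as total or direct, and two of the four eligible models condition on post-birth variables, of which the SAP's own text supports at least the respiratory ones as downstream of preterm birth. For a total effect, Models 3 and 4 are over-adjusted. The expected shift is toward the null, by about 25% to 75% with a total effect of −0.20 SD, mediator effects of −0.1 to −0.3 SD and no shared unmeasured cause. With such a cause it can go either way. Models 1 and 2 are free of this particular problem. The extra type I error from choosing among models is small by comparison, about 0.07 to 0.08 per contrast in simulation against the stated 0.05.

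**What to change.** In the Hypothesis and Primary analyses sections, state that the target is the total association of gestational age with cognition. Name Model 2, which has no neonatal or pubertal variable, as the single model for the primary 0.05 test and for any claim of independent association, and say that Table 2 reports it as such. Label Models 3 and 4 as secondary explanatory (mediator-adjusted) models that do not decide whether an association exists.

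Two details of Model 2 should be settled at the same time. Decide in advance whether C-section, a delivery event, stays in the maternal block, for example with a sensitivity analysis that omits it; omitting it changes the maternal MCA components and therefore Models 2 to 4 in that analysis. Describe SES as a current measure used as a proxy for circumstances around birth.

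The cost is SAP wording plus, if chosen, one sensitivity analysis. The downside is that the mediator-adjusted models can no longer support the headline claim.

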### **Primary analyses:**

- Linear regression model will be used to investigate whether the one-factor (intelligence) differ between preterm birth, early-term birth and full-term birth (presented as standardized beta and 95% CI)

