## Methods

### Participants

The neuroimaging and behavioural data used in this study will be obtained from the ABCD Study (data release 5.0; <https://abcdstudy.org/>; <http://doi.org/10.15154/1523041>), a longitudinal cohort of 11,875 children born between 2005 and 2009. These children were enrolled at ages 9-11 years from 21 research sites across the U.S. between 2016 and 2018, with the intention of following them for a period of at least 10 years. This recruitment cohort closely matches the sociodemographic composition of the US population of 9-11-year-old children. Most of the children were enrolled through local elementary and charter schools at each data-collection site. A smaller portion was recruited through community outreach and word-of-mouth referrals outside of the school setting. Twins were identified and recruited from birth registries.

During each visit, children accompanied by a parent/guardian, completed a series of measures. These included neurocognitive tests, mental and physical health questionnaires, environmental exposure data collection, providing biological specimens, and participating in brain imaging. All were asked for an in-person assessment session for self- or parent-report of mentioned behavioural measures and for biological specimen collections once a year, with brain imaging conducted biannually. For this study, we will use data collected between 2016 and 2018.

Children were excluded if they were born extremely preterm (< 28 weeks of gestation) or had birth weight (< 1200 g), were not proficient in English, had any neurological problems, had a history of seizures, or had a contraindication to undergo brain MRI scans. All children and their parents/guardians provided informed written consent/assent for participation, and the central Institutional Review Board at the University of California, San Diego approved the study protocols. All the research methods were performed in accordance with the relevant guidelines and regulations.

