### Polygenic Score Derivation and Analyses

#### Genotyping, quality control, and imputation

Saliva samples were collected from all the children during the T0 visit and genotyped using Rutgers University Cell and DNA repository using the Smokescreen array consisting of 646,247 genetic variants.

Quality control, imputation, and genetic PCA were performed by the National Bioinformatics Infrastructure Sweden (NBIS). The following pre-processing steps were conducted. Briefly, single nucleotide polymorphisms (SNPs) with call rates < 98% or minor allele frequencies (MAFs) < 1% were excluded before imputation. Individuals with high rates of missingness (> 2%) and absolute autosomal heterozygosity > 0.2 were excluded, resulting in 10,069 children and 430,622 genetic variants. Haplotypes were prephased using SHAPEIT2, and genetic markers were imputed using IMPUTE4 software.

We utilized the 1000 Genomes haplotypes—Phase 3 integrated variant set release in NCBI build 37 (hg19) coordinates as reference populations. This dataset consists of 2504 samples and 5008 haplotypes from Europeans, Africans, East Asians, Southern Asians, and Americans ([https://mathgen.stats.ox.ac.uk/impute/1000GP\\_Phase3.html](https://mathgen.stats.ox.ac.uk/impute/1000GP_Phase3.html)). We used this imputation since it

provides better concordance in diverse human populations. After that, genotypes with an INFO score < 0.3 or MAF < 0.001% were excluded, which yielded 40,637,119 SNPs in a total of 10,069 children.

The PCA module, as implemented in RICOPILI, was used to check for outliers and control population structure. SNPs were pruned so that there was little linkage disequilibrium (LD) between SNPs ( $R^2 < 0.2$ , 200 SNP window: Plink–indep-pairwise 200 100 0.2). LD pruning was repeated until 100 K SNPs were reached. The resulting SNPs were then projected into the PCA. We utilized the first 20 principal components (20PCs) from the genetic PCA.

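### The cohort includes twins, but the planned linear regressions have no family term or clustered variance, so standard errors are too small; multiple birth is also a possible confounder left out of the covariates

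*SAP*

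**What the plan says.** **Sample.** SAP, Participants, describes "a longitudinal cohort of 11,875 children born between 2005 and 2009" and adds: "Twins were identified and recruited from birth registries". The exclusions begin "Children were excluded if they were born extremely preterm (< 28 weeks of gestation) or had birth weight (< 1200 g" and go on to English proficiency, neurological problems, seizures and MRI contraindications. None removes twins or limits a family to one child. The genotype quality control in the Appendix filters on call rate, allele frequency, missingness and heterozygosity, "resulting in 10,069 children and 430,622 genetic variants". No relatedness filter is listed.

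**Model.** The Statistics section opens with: "Hierarchical logistic/linear regression model will be used to investigate the relationships between preterm birth and behavioural/brain outcomes". It then lists four models. The first is "Model 1: Adjusted for age of child, sex, SES, Polygenic scores, 20 PCs, and scanner sites"; the later ones add maternal, neonatal and child factors in turn. Primary analyses states: "Linear regression model will be used to investigate whether the one-factor (intelligence) differ between preterm birth, early-term birth and full-term birth". Secondary analyses uses the same type of model for the cognitive domains.

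**Covariates.** The only grouping variable is site: "Scanner sites as recommended by ABCD". Neither the maternal nor the neonatal list contains an item for multiple birth. Exploratory analyses names only sex and birthweight. The primary test is at 0.05 without correction.

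**The concern.** Linear regression with its usual standard errors treats every child as an independent observation. Two co-twins are not independent. They have the same gestational age, so they always fall in the same exposure group, and their cognitive scores are positively correlated; the SAP's Introduction itself calls cognitive ability largely heritable. When exposure is constant within a cluster and the outcome is positively correlated within it, the usual standard error of the exposure effect is too small. The direction is therefore known even though the size is not.

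Every primary and secondary interval and p-value is affected. The primary test has no multiplicity correction that might offset the inflation. The problem is greatest where twins are most common, which is plausibly the preterm groups.

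A second, separate issue is that a twin pregnancy precedes the birth and can shorten gestation. If twins differ from singletons in cognition for reasons other than gestation, a model without a multiple-birth term assigns that difference to preterm birth. This matters because the hypothesis is that preterm birth is independently associated with poorer cognition.

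**Working it through.** The SAP states no sample size, power or design effect for these analyses, so there is no figure to reproduce. What follows illustrates the size.

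**Inputs**
- From the SAP: twins are present; the model is linear regression; alpha is 0.05 (two-sided assumed, because 95% intervals are reported).
- Assumed, not in the SAP: preterm share *p* = 10–20%; share of children in complete twin pairs, *t*ₚ = 20–60% among preterm and *t*ₜ = 5–10% among term children; residual within-pair correlation ρ = 0.3–0.7; twin–singleton difference in score δ = 0 to −0.3 SD.

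**Step 1: standard error.** With exposure shared within a pair, the variance of a group mean is inflated by 1 + *t*ρ. For a two-group contrast,

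SE ratio (correct/ordinary) = √{ [(1 + *t*ₚρ)/*p* + (1 + *t*ₜρ)/(1 − *p*)] / [1/*p* + 1/(1 − *p*)] }

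The total sample size cancels, so the result does not depend on whether 11,875 or 10,069 children are analysed.

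**Step 2: actual alpha** = 2 × [1 − Φ(1.96 / SE ratio)].

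| Setting | *p* | *t*ₚ | *t*ₜ | ρ | Variance ratio | SE ratio | Coverage of nominal 95% CI | Actual alpha |
|---|---|---|---|---|---|---|---|---|
| Low | 0.20 | 0.20 | 0.05 | 0.3 | (5.300 + 1.269)/6.250 = 1.051 | 1.025 | 94.4% | 0.056 |
| Middle | 0.15 | 0.40 | 0.10 | 0.5 | (8.000 + 1.235)/7.843 = 1.178 | 1.085 | 92.9% | 0.071 |
| High | 0.10 | 0.60 | 0.10 | 0.7 | (14.200 + 1.189)/11.111 = 1.385 | 1.177 | 90.4% | 0.096 |

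The ordinary standard error is therefore too small by 1 − 1/1.025 = 2.4% to 1 − 1/1.177 = 15.0%.

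**Step 3: simulation check.** With *p* = 0.15, *t*ₚ = 0.60, *t*ₜ = 0.10, ρ = 0.5, 10,000 children and 4,000 replicates, the rejection rate was 0.083. The formula gives 0.081. The Monte Carlo error is √(0.081 × 0.919/4,000) = 0.004, so the two agree.

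**Step 4: possible bias from omitting multiple birth.** Bias = δ × (*t*ₚ − *t*ₜ). If δ = 0 the bias is 0. For δ = −0.1, −0.2 and −0.3 SD with *t*ₚ = 0.60 and *t*ₜ = 0.10, it is −0.05, −0.10 and −0.15 SD. With *t*ₚ = 0.20 and *t*ₜ = 0.05 it is −0.015, −0.03 and −0.045 SD.

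**Limit of the illustration.** It compares preterm with all term children. The planned reference group is full-term, 39 weeks and above, with early-term as a separate group. The same formula applies to each planned contrast, but it needs that group's own twin share; the early-term contrast was not calculated.

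**The case against.** **The word hierarchical.** It can mean multilevel, in which case clustering might already be covered. The text does not bear this out: what follows is a sequence of covariate blocks, and no grouping level or random effect is named. If a multilevel model was intended, the SAP has to say so and name the family level, so the same edit is needed.

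**Covariate adjustment.** Model 1 includes SES, the polygenic score, 20 principal components and site, several of which are shared or similar within a pair. The residual correlation will be lower than the raw one. This stands, and it argues for caution about the upper end of the range. Nothing in the SAP suggests that adjustment removes the correlation.

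**The figures are assumed.** This also stands. A reader might infer that the type I error is known to be near 10%. The documents do not support that: they give no twin share and no correlation, and at the low end of the assumed range alpha is 0.056.

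**Confounding.** A reader might infer that the preterm estimates are confounded by multiple birth. The documents do not show it. They report no twin–singleton difference and no share of preterm births from multiple pregnancies, and the bias is zero if twin birth has no effect of its own. C-section, placental problems and maternal age in Model 2, and NICU in Model 3, may act as partial proxies, though Model 1 has none. Adjusting for plurality is also partly a choice of estimand, whereas the variance problem is an error in the analysis as written.

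**Conclusion.** The clustering point holds. Twins are in the sample by design, nothing removes co-twins, and the variance model assumes independence, so the primary and secondary intervals are too narrow and the tests anti-conservative. The direction follows from shared gestational age and positively correlated cognition. The size rests wholly on assumed twin shares, preterm share and correlation: standard errors about 2–15% too small, coverage about 94.4% down to 90.4%, and alpha about 0.056–0.096. These figures are for preterm against term and are illustrative only. This should be corrected before the analysis is run.

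The point about multiple birth is weaker. It is a plausible confounder missing from the covariate list, with an assumed bias of 0 to about −0.15 SD. The stronger statement, that preterm effects are confounded, goes beyond what the SAP shows.

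**What to change.** 1. Fit all primary and secondary models with a random intercept for family nested in site, or keep the linear models and use standard errors clustered on family. Apply this within each imputed data set and then pool. State in the Statistics section that hierarchical refers to the covariate blocks, or name the levels if a multilevel model is meant.
2. Add a multiple-birth indicator to the covariates from Model 1 on or, at least, pre-specify a singleton-only sensitivity analysis.
3. Report the number of twin pairs in each gestational-age group, so that readers can judge the size of the effect.

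The cost is a few sentences in the SAP and a modest change to the code, repeated across four models and several outcomes. Family structure should also be considered when the imputation is set up. The statistical downside is slightly wider intervals; a singleton-only analysis also loses sample size. Fixing the handling in advance keeps it from being chosen after the results are seen.

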### **Secondary analyses:**

- Linear regression model will be used to investigate whether the general cognitive abilities, executive functions, and working memory performance differ between preterm birth and full-term birth (presented as standardized beta and 95% CI)

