### **Exploratory analyses:**

Sex and birthweight

Primary analysis will be uncorrected with statistical significance at 0.05. Secondary analysis will be adjusted for multiple comparison corrections.

All analysis will be carried out using R studio.

242 **Planned Figures and Tables**

243 Table 1 Demographics of maternal and child characteristics

244 Table 2 Results from the primary analysis

245 Table 3 Results from the weeks of gestation

246

247 Figure 1 Results of PCs.

248 Figure 2 Outcomes

249

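### Both aims ask how much of the association is explained, but the SAP plans no estimate of the change between models, no interval for it, and no step that isolates SES or the polygenic score

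*SAP*

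**What the plan says.** Under Study objectives, each of the two aims has two halves. The first is an association, with preterm and early-term birth in one aim and weeks of gestation in the other. The second is to "assess the extent to which these associations can be explained by unmeasured genetic and environmental factors".

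The Statistics section sets a nested sequence: "Model 1: Adjusted for age of child, sex, SES, Polygenic scores, 20 PCs, and scanner sites; Model 2: Model 1 + Maternal factors". It continues: "Model 3: Model 2 + Neonatal factors; Model4: Model 3 + child factors".

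The effect output is given under Primary analyses as "whether the one-factor (intelligence) differ between preterm birth, early-term birth and full-term birth (presented as standardized beta and 95% CI", and in the same format under Secondary analyses ("working memory performance differ between preterm birth and full-term birth (presented as standardized beta and 95% CI"). The planned tables cover demographics, the primary results and the weeks-of-gestation results.

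The SAP does not define a change in beta, a proportion explained, an incremental R-squared or an indirect effect. It gives no standard error, test or interval for a difference between models.

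**The concern.** In a nested sequence, the natural measure of how much a block explains is the change in the birth-group coefficient when that block is added. The plan gives each coefficient an interval but gives the change none. A reader left with only the separate intervals has no sound way to judge whether an attenuation is real or how precisely it is known.

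Three features of the sequence add to the problem:

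- No model precedes Model 1, which already holds SES, the polygenic score and the 20 components. The genetic and SES shares, central to both aims, cannot be read from any planned step.
- The aims speak of unmeasured factors, while every model adjusts for measured ones.
- Neonatal factors and puberty arise after birth. A change at Model 3 or 4 may be mediation, which is a different answer from confounding.

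At stake is the second half of each aim: it would end in statements about explanation with no planned estimate of precision.

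**Working it through.** **Is there a figure to reproduce?** No. The SAP states no sample size, power or effect size for this analysis. The check is of the statistical argument, by formula and simulation.

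**Formula.** For the birth-group coefficients b1 (before a block is added) and b2 (after), fitted to the same children with correlation r:

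SE(b1 − b2) = √(SE1² + SE2² − 2·r·SE1·SE2)

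Treating the two intervals as independent sets r = 0 and gives √(SE1² + SE2²). The per-model output supplies SE1 and SE2 but not r.

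**Input from the SAP.** N = 10,069, the genotyped sample ("which yielded 40,637,119 SNPs in a total of 10,069 children").

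**Assumptions, not in the SAP.** A smaller N of 5,000 as an alternative; exposed share 5% or 12%; direct effect −0.15; covariate block shifted by 0.3, 0.5 or 0.8 SD in the exposed, with effects of 0.05, 0.10 or 0.15 per SD on the outcome; residual SD 0.9. This makes 12 scenarios of 600 runs each. Families and imputation were not simulated.

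**One scenario in full** (N = 10,069, 12% exposed, middle block):

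- b1 = −0.199 and b2 = −0.149, a change of 0.050 in size. SE1 = 0.0278, SE2 about 0.0279, r = 0.982.
- By the formula: √(0.0278² + 0.0279² − 2 × 0.982 × 0.0278 × 0.0279) ≈ 0.0053. The simulated SD of the change was 0.0054.
- Treated as independent: 0.0394, which is 7.3 times larger.
- Paired 95% CI for the change: 0.050 ± 1.96 × 0.0054, or 0.039 to 0.061.
- Independent version: 0.050 ± 1.96 × 0.0394, or −0.027 to 0.127. A clear change looks like none.

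**All 12 scenarios:**

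| Quantity | Range |
|---|---|
| Correlation of b1 and b2 | 0.951 to 0.996 |
| True SE of the change | 0.0033 to 0.0143 |
| SE if treated as independent | 0.039 to 0.084 |
| Ratio of the two | 4.5 to 16.7 |
| Power with the paired SE | 0.86 to 1.00 |
| Power with the independent SE | 0.00 in eight, 0.002 in one, 0.67 to 1.00 in three |
| Runs in which the two CIs overlap | 99.8% to 100% in eleven, 18% in one |

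The 18% belongs to the largest change (about 0.12) at N = 10,069 with 12% exposed.

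**A separate simulation** (n = 10,069, assumed shares and effects) gave a preterm beta of −0.151 then −0.121, SE 0.030 each and r = 0.99. The formula gives 0.030 × √(2 × 0.01) = 0.0042, and the simulated value was 0.004. The change of 0.030 is therefore about 7 SE (0.030 / 0.0042). The two CIs, −0.210 to −0.092 and −0.180 to −0.062, overlap widely.

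**Why the absolute change and not a percentage.** With an assumed early-term beta going from −0.040 to −0.030, the change of 0.010 has SE 0.0023, about 4.3 SE. The ratio is unstable because its denominator is near zero (0.040 / 0.0226 ≈ 1.8 SE). Two simulations gave 95% sampling ranges of −153% to 146% and 7% to 169%.

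**The sequence itself.** Models 1 to 4 yield three steps: maternal, neonatal and child factors. None of them adds SES, the polygenic score or the components.

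**The case against.** The strongest reply is that the SAP makes no error in what it states. A reader might infer that it plans to judge attenuation by overlap of intervals, or to print a percentage from two betas. It says neither. Each interval is correct for its own model, and the Hypothesis section asks whether preterm birth is independently associated with cognition, which an adjusted beta with its CI does answer. The two point estimates also give the size of the change; only its precision is missing. All of this stands, and it makes the point an omission, not a wrong formula.

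It is also fair that an interval for adjacent-model changes would not by itself meet the aims, since the genetic and SES blocks are already in Model 1. That stands too, and it shapes the fix.

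The simulated sizes rest on assumed effects, and with a large enough change the intervals do separate. The direction does not depend on those choices: it follows from fitting both models to the same children.

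What the reply does not remove is that the aims ask for an extent. Followed to the letter, the plan leaves that half without an estimate of precision.

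**Conclusion.** The concern holds as a gap between the aims and the planned output. The second half of each aim has no defined quantity and no interval, and the SES and genetic shares cannot be obtained from the planned sequence. Under the assumed scenarios, per-model intervals taken as independent overstate the standard error of the change 4.5 to 16.7 times. They would usually hide a real change. They do not create a false one, so it would go too far to say that the planned output misleads in both directions.

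It would also go too far to call the early-term change noise: only the percentage is unstable, and the SAP plans none. The primary contrasts between birth groups, and the test of an independent association, are not affected. The change is one the sponsor should make; it does not invalidate the primary analysis.

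**What to change.** 1. Add a base model with age, sex and site. Enter SES, then the polygenic score with the 20 components, as separate steps before the maternal factors. Keep the neonatal and child steps after that. Fix the order in advance, because each step's share depends on it.
2. Fit all models on one fixed analysis sample. The cohort has 11,875 children and the genotyped set 10,069. A base model on the full cohort would differ by 1,806 children, and the change would then mix adjustment with selection.
3. For the preterm and early-term contrasts, and for weeks of gestation, report the absolute change in beta between named models with a 95% CI. Obtain it from a paired bootstrap that resamples families (twins were recruited), refits both models on each resample, and is combined across the imputed data sets.
4. Base every statement about explanation on that change and its CI. Do not print a percentage only when the starting beta is significant. With the early-term figures above and a true share of 25%, that rule gave a median of 17%, with 94% of reported values below the truth.
5. Describe the factors as measured, and read changes from neonatal factors and puberty as possible mediation rather than confounding.

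The cost is SAP wording, computing time and extra table columns. No new data are needed.
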